### **7b. Secondary objectives and hypothesis**

Other PEM symptoms (muscle pain, joint pain, lymph nodes, concentration, memory, headache, fever, sore throat) will be assessed using VAS 0–10 before, after and 48h after 3 different types of exercise the post-COVID-19 patients and controls and compared between the groups. An additional 3 validated questionnaires are used: a) Multifunctional Fatigue Inventory (MFI), b) Profile of Mood States (POMS), and c) Somatic and Psychological Health REport (SPHERE) will be administered to participants before, immediate-, and 48h post-exercise to assess PEM. We hypothesize that the post-COVID-19 group will suffer from persistent fatigue at 48h after exercise compared to baseline, whereas control group will return to the baseline level at this time point.

Cardiopulmonary exercise testing (CPET) will be also performed in post-COVID-19 subjects and age/sex matched controls at 48 hours post different exercise trials to assess and compared the exercise (in)capacity. Peak volume of oxygen consumption ( $\text{VO}_{2\text{peak}}$ ), and other parameters, including ventilation and  $\text{VE}/\text{VCO}_2$  ratio,  $\text{O}_2$  saturation, heart rate, blood lactate, and rating of perceived exertion (RPE) using Borg scale will be also used to assess exercise capacity in all participants at 48 hours following each exercise trial. We hypothesize that post-COVID-19 group may have lower exercise capacity at 48h compared to controls.

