## **11. INTERVENTIONS**

### **11a. Description of interventions for each group**

#### Exercise response

Subjects will perform high-intensity-interval training (HIIT), moderate intensity continuous exercise (MICT) and strength training (ST). The acute exercise responses will be closely monitored, including measurements of O2 saturation, heart rate, blood pressure, rating of perceived exertion (Borg scale 6–20) and blood lactate. In addition, symptoms via multiple validated questionnaires and blood samples will be collected before, immediately after each exercise session to describe leukocyte and cytokine release. After a 48-hour rest period subjects will return to the laboratory for symptom assessment, submaximal exercise response (CPET), and blood sampling.

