## 12. EXPLANATIONS OF THE ASSESSEMETNS – OUTCOMES

### Exercise trials (HIIT, MICT, ST)

Subjects will perform 5 minutes warm-up, then either of the following exercise training protocols in a randomized order, followed by 5 minutes of active recovery. **MICT:** Continuous 30 min cycling at moderate intensity **HIIT:** 5 x 1 min cycling at high intensity, 1 min rest **ST:** 3 sets x 10 repetitions of 3 exercises covering large muscle groups of the lower and upper body (2 min recovery between sets). Exercise sessions will be thoroughly and continuously monitored, including measurements of O2 saturation, blood pressure, and blood lactate. In addition, blood samples will be collected before, immediately after, 1h and 48h post each exercise session to describe leukocyte and cytokine release. At 48 hours follow up, post-exercise symptoms and exercise responses to a monitored graded exhaustion test will also be reported.

**HIIT session:** 5 x 1-min intervals on a cycle ergometer (Monark LC6, Vansbro, Sweden) with a workload equal to 90% of the workload the patients achieve during the initial cardiopulmonary exercise testing (CPET) at baseline. Each interval will be interrupted by a 1-minute rest period in a seated position. Intensity is increased to be  $\geq 16$  on the Borg scale at the end of the session. The workload is increased if the perceived exertion is lower and decreased if subjects are unable to achieve an RPM above 55.

**MICT session:** 30 minutes of continuous cycling (Monark LC6, Vansbro, Sweden). Participants will be asked to cycle at 50% of the workload achieved during the baseline CPET. The intensity aims to correspond to 12–14 according to the Borg scale. If the rating is lower, the workload is increased and vice versa if the rating is higher. The monitoring of RPE is done every five minutes during the training session.

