## **20. STATISTICAL METHODS**

Analyses will be performed using IBM SPSS Statistics for Windows, version 29.0 (Armonk, NY: IBM Corp). To assess the primary outcome (post-exertional symptom exacerbation from baseline to 48h after each exercise), a mix-linear model was initially planned to analyse the differences in symptom changes following three exercise sessions (HIIT, MICT, ST), between the two groups (post-COVID-19 patients vs. control). Subject ID and the order of exercise sessions will be used as random effect in the mix-linear model. Pairwise comparisons will be performed when significant main or interaction effects are detected, using Bonferroni correction.

However, during data analysis, the aforementioned statistical plan was amended given the nature of the data (not normally distributed data). Particularly, a significant number of the control subjects responded “zero” change in the visual analog scale assessing the symptom exacerbation. As such, non-parametric tests (Mann-Whitney test, Kruskal-Wallis test) were used to compare differences in symptoms following exercise trials between the groups.

A mixed-linear model was used to analyze differences in continuous data (CPET variables, interleukin (IL)-6, Creatine Kinase) following three exercise sessions (HIIT, MICT, ST) between the two groups (post-COVID-19 patients vs. control). Subject ID and order of exercise sessions were used as random effect in the mix-linear model. Pairwise comparisons will be performed when significant main or interaction effects are detected, using Bonferroni correction.

For the physiological characterization assessments, two-tailed Chi-square test or Student t-test will be used to examine differences in categorical or continuous variables, respectively, between the post-COVID-19 patients and the control group.

Results will be presented as mean (SD), and significance will be set at  $P < 0.05$ .

Missing data will be treated as missing values in the statistical models, unless otherwise specified. In retrospect, there was no need for missing data imputation. Therefore, missing data were treated as missing values.

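### The 48-hour CPET comparison is framed as a group difference in level with no stated use of the baseline CPET, so a fitness gap present beforehand could be misread as an effect of the exercise sessions

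*Combined protocol and SAP*

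**What the plan says.** Section 7b says that CPET "will be also performed in post-COVID-19 subjects and age/sex matched controls at 48 hours post different exercise trials", lists VO2peak among the measures, and gives the hypothesis "We hypothesize that post-COVID-19 group may have lower exercise capacity at 48h compared to controls". This is a comparison of levels after exercise.

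Section 20 gives the analysis: "A mixed-linear model was used to analyze differences in continuous data (CPET variables, interleukin (IL)-6, Creatine Kinase) following three exercise sessions", between the two groups. It adds: "Subject ID and order of exercise sessions were used as random effect in the mix-linear model". No baseline term or change score is named. No analysis scale is given for IL-6 or creatine kinase.

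A baseline CPET exists for those who do the sessions, because Section 12 sets workloads from it. For the moderate session: "Participants will be asked to cycle at 50% of the workload achieved during the baseline CPET". Its other stated use is the physiological characterization in Section 7b, where Section 20 plans a separate t-test between groups.

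The 48-hour test is described in two ways. In Section 11a, "subjects will return to the laboratory for symptom assessment, submaximal exercise response (CPET), and blood sampling". In Section 12, "post-exercise symptoms and exercise responses to a monitored graded exhaustion test will also be reported".

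**The concern.** The first aim in Section 6b asks whether patients have physical limitations following exercise. That is a question about change. The protocol treats its primary outcome that way: Section 7a compares the change in fatigue from before to 48 hours after each session. The CPET hypothesis drops the reference to baseline.

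Only session order is randomized. Being a patient or a control is not, so randomization gives no protection against a difference in fitness at entry. Section 6a itself cites a cohort in which exercise capacity was reduced in all patients. If patients start lower, they will also be lower at 48 hours even when the sessions do nothing. A group difference at 48 hours cannot tell the two situations apart. Two separate tests, one at baseline and one at 48 hours, do not show whether the gap widened.

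**Working it through.** **The plan's own figure.** There is none for this comparison. The 28 per group in Section 14 is for a within-between interaction and does not bear on it.

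**Inputs from the documents.** Two groups; one baseline CPET; three 48-hour CPETs per person; two-sided 5%. Group size is 28 (Section 14, minimum), 30 (Section 9) or 40 (Synopsis), so all three are shown.

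**Assumptions, not in the documents.** Within-group SD of one CPET value = 1. Correlation between any two tests (ICC, written r) = 0.8 or 0.9. Prior gap d = 0.3, 0.5 or 0.8 SD. True exercise effect = 0.

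**Variances.**
- Mean of three 48-hour tests: r + (1 − r)/3. For r = 0.8 this is 0.867 (SD 0.931); for r = 0.9 it is 0.933 (SD 0.966).
- That mean minus baseline: (1 − r) × 4/3. For r = 0.8 this is 0.267 (SD 0.516); for r = 0.9 it is 0.133 (SD 0.365).
- Ratio of SDs: 0.931/0.516 = 1.80 and 0.966/0.365 = 2.65.

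**False signal, 48 hours only.** With no exercise effect the expected group difference at 48 hours is the whole prior gap, −d. The rejection probability comes from a noncentral t with 2n − 2 degrees of freedom and noncentrality (d/SD) × √(n/2). Example: n = 30, d = 0.5, r = 0.8 gives 0.5/0.931 × 3.873 = 2.08 against a critical value of 2.00, so 53.4%.

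| n per group | r | d = 0.3 | d = 0.5 | d = 0.8 |
|---|---|---|---|---|
| 28 | 0.8 | 22.0% | 50.6% | 88.4% |
| 28 | 0.9 | 20.7% | 47.7% | 86.1% |
| 30 | 0.8 | 23.3% | 53.4% | 90.5% |
| 30 | 0.9 | 21.9% | 50.5% | 88.4% |
| 40 | 0.8 | 29.6% | 66.0% | 96.7% |
| 40 | 0.9 | 27.9% | 62.8% | 95.5% |

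With d = 0 the rate is 5%. For change from baseline the gap cancels and the rate is 5% at every d; simulation with 6,000 runs per scenario, at 30 and 40 per group, gave about 5% throughout.

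**Power for a real effect.** Take no prior gap and a true extra fall of 0.3 SD in patients, n = 30. For change, noncentrality is 0.3/0.516 × 3.873 = 2.25 (power 60%) at r = 0.8, and 0.3/0.365 × 3.873 = 3.18 (88%) at r = 0.9. For 48 hours only, power is 23% and 22%. Those are the d = 0.3 entries in the table: to that analysis, a gap of 0.3 SD beforehand and a fall of 0.3 SD afterwards are the same thing.

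**Covariate adjustment alone.** Adjusting the 48-hour mean for baseline leaves a bias of about (1 − r) × d when groups differ at entry. At d = 0.8 this is 0.16 SD (r = 0.8) or 0.08 SD (r = 0.9). Simulated false-positive rates were 22% and 13% at n = 30, and 28% and 16% at n = 40.

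**Limit of the change analysis.** If retest effects differ between groups by an assumed 0.2 SD, change from baseline is significant in 31% (r = 0.8) or 55% (r = 0.9) of trials at n = 30 with no exercise effect.

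**The case against.** Section 20 is a short description. It is silent on baseline and does not exclude it, so a reader who infers that baseline was deliberately left out goes beyond the text. What stands is that neither the hypothesis nor the model mentions it.

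Section 9 says controls are matched on physical fitness as well as sex and age. Done on VO2peak, that would shrink the gap on which the table depends. But the Synopsis and Sections 7a, 7b and 8 give age and sex only, and no matching procedure is described. Matching would also leave residual imbalance and the loss of precision.

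The hypothesis claims only a lower level, and the separate baseline comparison would let readers see a deficit. It is therefore too strong to say that a deficit would be reported as caused by exercise; it could be misread that way.

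A constant gap biases the group difference and between-group pairwise contrasts. It does not bias group-by-session or within-group contrasts between sessions, so part of the planned analysis is unaffected.

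The move of the symptom scores to non-parametric tests may suggest that IL-6 and creatine kinase were fitted on the raw scale. The documents do not say so; the scale is simply not stated.

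**Conclusion.** The point holds for the group difference in CPET at 48 hours. As written, the hypothesis and model do not separate lower fitness beforehand from lower capacity after the sessions. At 30 per group, with no exercise effect, false signals arise in about 22–23%, 51–53% and 88–91% of trials for prior gaps of 0.3, 0.5 and 0.8 SD. The corresponding figures are 21–22%, 48–51% and 86–88% at 28 per group, and 28–30%, 63–66% and 96–97% at 40. The gaps and the ICC of 0.8–0.9 are assumptions; with no gap the rate is 5%. The SD of change is 1.8 to 2.6 times smaller, a gain that does not depend on a gap being present. The 5% rate for change requires equal retest effects in the two groups. CPET is a secondary outcome, so the primary fatigue analysis is not touched.

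The two descriptions of the 48-hour test contradict each other. This is a separate documentation fault, but it matters here because baseline and 48-hour values compare only if the test is the same.

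**What to change.** - Restate the hypothesis as a greater fall from baseline CPET to 48-hour CPET in patients than in controls.
- Enter baseline CPET as a time level and test group by time, naming the contrast of the 48-hour tests with baseline; or analyse change from baseline. Do not rely on covariate adjustment alone, because the groups are not randomized. If baseline was already used, say how.
- Use pre-session IL-6 and creatine kinase values in the same way. State their analysis scale, with log transformation if they are skewed.
- State as a limitation that baseline is always the first CPET and that no 48-hour test without prior exercise exists, so familiarisation or time effects that differ between groups remain.
- Reconcile Section 11a with Sections 7b and 12 on what the 48-hour test is, and the statements on fitness matching.
- Of lesser weight: enter period as a fixed effect with subject random. Three sessions give three positions or six sequences, few levels for estimating a random-effect variance.

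The cost is revised wording and a re-run on data the protocol already collects, with no new visits. Period as a fixed effect uses 2 degrees of freedom.

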## **8. TRIAL DESIGN**

This is a prospective interventional randomized two-arm crossover designed study. Two experimental groups: a) post-COVID-19 syndrome patients and b) age- and sex-matched healthy controls performed 3 different exercise sessions in a randomized counterbalanced order. Researchers will be blinded during the data analysis and during the data collection as far as possible.

## **9. METHODS: PARTICIPANTS, INTERVENTIONS AND OUTCOMES**

Thirty post-COVID-19 patients will be recruited through the post-COVID-19 clinic at Karolinska University Hospital Huddinge or other channels (advertisements posted on the Karolinska Institute website, social channels, information boards, and advertisements on the Swedish Post-COVID-19 patients' organization webpage and social channels. Interested participants contacted us for further information. Interested participants contacted us for further information Patients should be aged between 18–64 years, experienced persisting symptoms at least 3 months, including post-exertional exacerbation symptoms, and had no previous history of cardiovascular disease, general anxiety syndrome or somatic symptom disorder. In addition, 30 healthy control subjects, matched for sex, age and physical fitness will be also recruited from the community (advertisements posted on the Karolinska Institute website, social channels and information boards). All subjects will perform a comprehensive set of physiological assessments, including COVID-19-related symptoms, post-exertional symptoms, neurophysiological function, cardiovascular and circulatory function, respiratory/ventilatory function, maximal oxygen uptake, muscle strength, physical function, blood status, and cytokine profiling. Subjects will then complete 3 exercise trials in a randomized counterbalanced order: continuous moderate-intensity training (MICT), high-intensity interval training (HIIT), and strength training (ST). The acute exercise response will be thoroughly and continuously monitored, including measurements of O2 saturation, blood pressure, ventilatory response, oxygen uptake, and blood lactate. In addition, blood samples will be collected before, immediately after, and 1 hour after each exercise session to describe leukocyte and cytokine release. After a 48-hour rest period following each exercise session, patients will return to the laboratory for symptom assessment, graded exercise testing, and blood sampling. Finally, after 1 year, we will perform a physiological follow-up using the same measurements as the baseline examination. Figure 1 shows the study design divided into two main parts, physiological assessment (A; comprehensive physiological characterization and 1 year follow-up, B; acute exercise sessions).

[figure not shown]

**Figure 1:** Study design, including physiological (characterization) assessments spread into 3 visits (A) and acute exercise sessions (B). Same assessments as in (A) will be conducted at 1-year follow up.

PBMCs: peripheral blood mononuclear cells; VAS: Visual analog scale; MFI: Multifunctional Fatigue Inventory; POMS: Profile of Mood States; SPHERE: Somatic and Psychological Health Report; MICT: moderate-intensity continuous training, HIIT: high-intensity interval training, ST: strength training, CPET: cardiopulmonary exercise testing

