| PRIMARY OBJECTIVE  | Post-exertional malaise (PEM)
symptoms of post-COVID-19 subjects
and age/sex matched controls in
response to 3 different exercise trials.                                                                                                                                                                                                                                                                                                                                                                                           |
| STUDY DESIGN       | Interventional, randomized, single-
center, two-arm crossover study                                                                                                                                                                                                                                                                                                                                                                                                                                                                       |
| STUDY ARMS         | 
1) Post-COVID-19 syndrome patients
 
2) Age- and sex-matched healthy control
subjects
                                                                                                                                                                                                                                                                                                                                                                                                                                        |
| SAMPLE SIZE        | 40 post-COVID-19 syndrome patients
and 40 age- and sex-matched healthy
controls                                                                                                                                                                                                                                                                                                                                                                                                                                                        |

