## **7. OBJECTIVES**

### **7a. Primary objective and hypothesis**

Post-exertional malaise (PEM) symptoms of post-COVID-19 subjects and age/sex matched controls in response to three different exercise trials. The primary outcome is the comparison of the change in fatigue rating using the visual analog scale (VAS) 0-10 before and 48h after each training trial between the post-COVID-19 group and the control group. We hypothesize that the post-COVID-19 group will suffer from persistent fatigue at 48h after exercise compared to baseline, whereas control group will return to the baseline level at this time point.

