Physiological (comprehensive) characterization post-COVID-19 subjects and comparison with age/sex matched controls will provide knowledge on the physiological phenotype of the post-COVID-19 group. Numerous clinical examinations will be used to assess the physiological function of post-COVID-19 patients and compared to age/sex matched controls. Specifically, echocardiography and arteriography will be used to assess cardiovascular function, spirometry to assess respiratory function, cardiopulmonary exercise testing and 6-min walk test to assess exercise capacity, handgrip and isokinetic dynamometer to assess the muscular strength of upper and lower body respectively, CO-rebreathing method to assess blood and plasma volume, and head up tilt-test to assess dysautonomia. In addition, neurophysiological assessment includes nerve conduction studies, sympathetic skin response, heart rate variability studies, and needle EMG. Questionnaires, blood samples and muscle biopsy will be also collected and compared between the groups.

Finally, physiological function at 1y follow-up in post-COVID-19 patients and age/sex matched controls will be assessed. Same clinical investigations as the

baseline assessment will be performed at 1y follow-up in post-COVID-19 patients and age/sex matched controls. Comparisons within and between groups from baseline and 1y follow-up will be performed.

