## **18. DATA COLLECTION**

At baseline and at 1-year follow-up, all physiological variables will be assessed under strictly standardized procedures in a laboratory setting. Physiological functions of the patients with post-COVID-19 condition will be compared with a well-matched healthy control group in an exploratory manner, as this patient population has yet to be characterized. Measurements before and after 1 year will be compared to determine if improvements are more related to certain physiological factors than others. Figure 1 and section 12 provide details in regards to the data collection for each particular outcome.

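### Matching variables conflict across sections and no analysis uses them: tests of age- and sex-dependent continuous outcomes are conservative, and capacity differences are attenuated only if current fitness was matched

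*Combined protocol and SAP*

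**What the plan says.** **Matching.** Section 9 has "30 healthy control subjects, matched for sex, age and physical fitness will be also recruited from the community". The synopsis has "40 age- and sex-matched healthy" controls, Section 7a has "Post-exertional malaise (PEM) symptoms of post-COVID-19 subjects and age/sex matched controls in response to three different exercise trials", and Section 8 has "age- and sex-matched healthy controls performed 3 different exercise sessions in a randomized counterbalanced order". The brief summary and Section 7b also name age and sex only. Section 18 says that patients' physiological functions "will be compared with a well-matched healthy control group in an exploratory manner", without naming the variables. Nowhere does the plan define fitness, say whether it means fitness now or before the illness, give a tolerance, or say whether matching was by individual pair or by group frequency.

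**Capacity as an outcome.** Section 7b lists "cardiopulmonary exercise testing and 6-min walk test to assess exercise capacity" among the baseline comparisons, together with strength, blood volume and spirometry, and repeats them at one year. For the test two days after each session it says: "We hypothesize that post-COVID-19 group may have lower exercise capacity at 48h compared to controls".

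**Analysis.** For the characterization, Section 20 says "two-tailed Chi-square test or Student t-test will be used to examine differences in categorical or continuous variables". Symptoms are compared with Mann-Whitney and Kruskal-Wallis tests. CPET variables, IL-6 and creatine kinase go into a mixed model whose random effects are subject and session order. No listed analysis has a term for age, sex, fitness or matched pair.

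**The concern.** Being a patient or a control is not randomised; Section 16 randomises only the order of the sessions. Beyond the eligibility criteria, matching is the only protection against confounding that the plan states, so its definition matters.

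Two consequences follow. First, matching balances age and sex between the groups, but an analysis that omits them leaves their variation in the error term. The reported standard error is then larger than the true one, and real differences in strongly age- and sex-dependent measures are harder to detect. Second, Section 6a cites a study in which every patient had reduced exercise capacity, and it lists deconditioning among the candidate mechanisms. If controls were chosen to resemble patients' fitness as it is now, part of the difference that Section 7b sets out to measure has been removed by recruitment.

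**Working it through.** The plan gives no figure on this point. Its one calculation, the 28 per group in Section 14, does not enter here. The shares of variance, correlations and effect sizes below are assumptions, because the documents give none.

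**1. Loss from omitting age and sex.** Let R² be the share of outcome variance explained by age and sex, and suppose matching has balanced both. The unadjusted standard error uses the whole variance and the adjusted one uses the fraction 1 − R². Apart from two degrees of freedom (58 against 56 at 30 per group), the ratio of interval widths is 1/√(1 − R²):

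| R² | 1/√(1 − R²) | Excess width |
|---|---|---|
| 0 | 1.00 | none |
| 0.1 | 1/√0.9 = 1.05 | 5% |
| 0.3 | 1/√0.7 = 1.20 | 20% |
| 0.5 | 1/√0.5 = 1.41 | 41% |

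Simulation with group matching, no pair identifiers, 30 per group (the number in Section 9) and a standardized difference of 0.5 agrees:

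| R² | Width ratio | Power, unadjusted | Power, adjusted | Type I error, unadjusted |
|---|---|---|---|---|
| 0.1 | 1.05 | 0.48 | 0.52 | 0.041 |
| 0.3 | 1.19 | 0.48 | 0.63 | 0.020 |
| 0.5 | 1.41 | 0.48 | 0.77 | 0.008 |

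The adjusted type I error was 0.052 to 0.055. The unadjusted test is therefore conservative, not invalid, and its point estimate is unbiased. The loss does not need individual pairs.

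The same reasoning applies to the group level contrast in the mixed model, with R² read as the share of variance in a subject's average. The group-by-session interaction is a within-subject comparison, so constant age and sex effects on level cancel from it.

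**2. If individual pairs were formed.** With within-pair correlation r, 30 pairs and a difference of 0.5, unpaired against paired power is 0.48 v 0.46 at r = 0, 0.48 v 0.51 at r = 0.1, 0.47 v 0.61 at r = 0.3 and 0.47 v 0.75 at r = 0.5. Using the pairs gains nothing at r = 0, little at 0.1 and a material amount from about 0.2 to 0.3.

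**3. Attenuation if current fitness was matched.** Let D be the true standardized capacity difference, s the patients' shift on the matched fitness measure, and ρ its correlation with the capacity outcome. The expected remaining difference is D − ρs.

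| ρ | Share of D left, s = D | Share of D left, s = ρD |
|---|---|---|
| 0.3 | 70% | 91% |
| 0.5 | 50% | 75% |
| 0.7 | 30% | 51% |
| 0.9 | 10% | 19% |

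Example with D = 0.8, ρ = 0.7 and 30 per group: for s = D, 0.8 − 0.7 × 0.8 = 0.24; for s = ρD = 0.56, 0.8 − 0.7 × 0.56 = 0.41. Power falls from 0.87 to 0.15 or 0.35. If matching used pre-illness fitness, or no fitness measure, this mechanism removes nothing.

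**The case against.** The strongest reply is that one sentence mentions fitness, while every other place that names the matching variables says age and sex. Section 9 has controls recruited by advertisement, with maximal oxygen uptake among the assessments that all subjects then undergo; it describes no selection on VO2peak. The 48-hour hypothesis of lower capacity in patients also sits badly with matching on current capacity. This stands. A reader might infer that the capacity contrasts are biased to zero whatever the disease does. The documents do not support that: it would need near-perfect matching on current VO2peak itself, and even matching on a correlated current measure leaves part of the difference.

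A reader might also infer that the primary result is compromised. It is a within-person change in fatigue VAS, and differencing removes stable age and sex effects on level, so the R² range above should not be carried over to it. Comparing symptom responses at similar fitness is also a defensible aim. The point gives no ground for replacing the non-parametric primary test.

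Nor does it follow that chi-square tests should become logistic models to gain precision. The width formula belongs to linear models; logistic adjustment generally does not shrink the standard error of the log odds ratio, and it changes the quantity estimated.

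Finally, omitting covariates is an inefficiency and not an error, and Section 18 calls the characterization exploratory. That limits the weight of the point but does not remove it: the plan still makes these comparisons, and the remedy is nearly free.

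**Conclusion.** The point holds in a limited form. The matching descriptions conflict, fitness is undefined, and no analysis uses the matching factors; all three can be read directly from the text.

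For continuous outcomes that depend on age and sex, the t-test and the mixed model's group level contrast are conservative. Intervals are about 5%, 20% or 41% wider than adjusted ones at R² of 0.1, 0.3 or 0.5. This rests on the assumed R² range and on matching having balanced age and sex. Estimates are not biased by it, and outcomes unrelated to age and sex lose nothing.

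Attenuation of capacity levels is conditional on matching on current fitness, which the documents do not establish. If it occurred, between 10% and 91% of the true difference remains over the ranges assumed. The plan does not propose to conclude that capacity is equal, so the risk lies in how a null result would be read.

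**What to change.** 1. State one set of matching variables in the synopsis, brief summary and Sections 7, 8, 9 and 18. If fitness was used, give the measure and whether it refers to current or pre-illness fitness. Say whether matching was by pair or by group.
2. For continuous characterization outcomes, fit a linear model with group, age and sex in place of the t-test. Add age and sex as fixed effects to the mixed model for CPET variables and biomarkers. Add a pair term only if controls were individually matched.
3. Sections 20 and 25 record that the analysis plan was already revised during data analysis. Report the adjusted results beside the unadjusted ones and label them as added post hoc.
4. If current fitness was matched, describe capacity level differences as attenuated: a null result is not evidence of no difference, while an observed deficit is conservative.

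The cost is revised wording and a few extra models. Age is an eligibility criterion and sex a matching variable, so both should already be on record and no new data are needed.
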